### Statistical analysis

The primary analysis will be of differences in hip-related quality of life (iHOT-33) at 12 months between the two treatment groups, blinded, on an intention-to-treat basis and presented as the mean difference between the trial groups with a 95% CI. iHOT-33 data will be assumed to be normally distributed; possibly after appropriate variance-stabilising transformation.

The minimisation randomisation procedure should ensure treatment group balance across recruiting sites. We have no reason to expect that clustering effects will be important for this study, but the possibility of such effects will be explored as part of the analysis.^33^ We plan to account for clustering by generalising a conventional linear (fixed-effects) regression approach to a mixed-effects modelling approach; where patients are naturally grouped by recruiting sites (random-effects) and, if amenable to analysis, also by physiotherapist and surgeon. This model will formally incorporate terms that allow for possible heterogeneity in responses for patients due to the recruiting centre, in addition to the fixed effects of the treatment groups, and patient characteristics that may prove to be important moderators of treatment effect such as age, gender and FAI type. This analysis will be conducted using specialist mixed-effects modelling functions available in the software packages Stata (StataCorp. 2015. Stata Statistical Software: Release 14. College Station, Texas, USA: StataCorp LP) and R (http://www.r-project.org/). All tests will be two-sided and considered to provide evidence for a statistically significant difference if p values are <0.05 (5% significance level).

Secondary analyses will be performed using the above strategy for other approximately normally distributed outcome measures, including iHOT-33 at 6 months, SF-12 (and computed subscales) and EQ5D. Differences in dichotomous outcome variables such as AEs, complications related to the trial interventions and the need for further procedures will compared between groups using χ^2^ tests (or Fisher's exact test) and mixed-effects logistic regression analysis will be undertaken, adjusting for the stratifying variables, with differences between trial intervention groups quantified as ORs (and 95% CIs). The temporal patterns of any AEs will be presented graphically and if appropriate, a time-to-event analysis (Kaplan-Meier survival analysis) will be used to assess the overall risk and risk within individual classes of AEs. Ordinal scores for patient satisfaction will be compared between intervention groups using proportional odds logistic regression analysis, assuming that the estimated intervention effect between any pair of categories is equivalent.

Our inferences will be drawn from the intention-to-treat analysis. We will perform two exploratory secondary analyses. One will compare patients who received surgery and those who received conservative care. A second exploratory analysis will compare patients randomised to surgery or PHT and received treatment deemed to be of a high fidelity by the respective review panels. We plan to perform a subgroup analysis by FAI type because it is possible that treatment effect is moderated by type. We anticipate that adequate steps have been taken to prevent crossovers from being a major issue for this study. Therefore, we expect the main intention-to-treat analysis to provide definitive results. An independent Data Monitoring Committee (DMC) will monitor crossovers and adherence to treatment and advise on appropriate modifications to the statistical analysis plan as the full trial progresses.

The initial feasibility and pilot studies (HTA 10/41/02) were designed explicitly to assess feasibility and measure recruitment rates, and not to estimate treatment effectiveness. Data from the pilot will be pooled with data from the full trial, and analysed together.

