**Methods:**

We will conduct a multicentre, pragmatic, assessor-blinded, two parallel arm, RCT comparing arthroscopic surgery to physiotherapy-led best conservative care. 24 hospitals treating NHS patients will recruit 344 patients over a 26-month recruitment period. Symptomatic adults with radiographic signs of FAI morphology who are considered suitable for arthroscopic surgery by their surgeon will be eligible. Patients will be excluded if they have radiographic evidence of osteoarthritis, previous significant hip pathology or previous shape changing surgery. Participants will be allocated in a ratio of 1:1 to receive arthroscopic surgery or conservative care. Recruitment will be monitored and supported by qualitative intervention to optimise informed consent and recruitment. The primary outcome will be pain and function assessed by the international hip outcome tool 33 (iHOT-33) measured 1-year following randomisation. Secondary outcomes include general health (short form 12), quality of life (EQ5D-5L) and patient satisfaction. The primary analysis will compare change in pain and function (iHOT-33) at 12 months between the treatment groups, on an intention-to-treat basis, presented as the mean difference between the trial groups with 95% CIs. The study is funded by the Health Technology Assessment Programme (13/103/02).

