### Participant identification, invitation, recruitment and baseline data collection

Patients who complain of hip pain, who do not already have a diagnosis of hip osteoarthritis, will be identified as potential participants by screening referral letters to collaborating surgeons. Research nurses/associates will keep accurate screening logs to identify if these potential participants meet the eligibility criteria. Once diagnosed with FAI syndrome by the surgeon, and deemed eligible for the trial, the patient will be given a trial information sheet (see online supplementary files 1 and 2) and referred to a trained recruiter for a trial information consultation. During this consultation, patients can discuss the trial, participation will be offered and informed consent obtained (see online supplementary files 3 and 4). It will be explained that participation is voluntary and patients can withdraw at any time. Once consent is obtained, and prior to treatment allocation, baseline patient reported outcomes will be collected (see the Outcome measures section).

10.1136/bmjopen-2016-012453.supp1Supplementary data

10.1136/bmjopen-2016-012453.supp2Supplementary data

10.1136/bmjopen-2016-012453.supp3Supplementary data

10.1136/bmjopen-2016-012453.supp4Supplementary data

In order to optimise recruitment and informed consent, trained qualitative researchers will observe recordings of the surgeons' and research associate/nurses' trial information consultations (see online supplementary files 2 and 4), to identify communication patterns that facilitate or hinder patient recruitment^15^ (see figure 1). In-depth interview with the recruiters will be undertaken to identify clear obstacles and hidden challenges to recruitment, including the influence of patient preferences and equipoise.^20^ Research teams will be interviewed to identify clinician equipoise, patient pathway from eligibility to consent and staff training needs at each participating site.^15^ Findings will be fed back to the CI and trial management group, so that practice can be reviewed and any necessary changes (including additional training) implemented. The number of eligible patients, the percentages of these that are approached and consented to be randomised will be monitored at each site.

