### Outcome measures

Baseline data will be collected from participants once consent is obtained and prior to randomisation. Follow-up questionnaires will be administered centrally by a data clerk via post. If participants fail to respond, they will be contacted via telephone, email or via their next of kin where necessary. Table 1 lists the data collected and at which follow-up time points.

**Table 1 BMJOPEN2016012453TB1:** Data collection time points

Time point	Data collection
Baseline	Demographics, physical activity (UCLA Activity Scale),^29^ iHOT-33, SF-12,EQ-5D Preoperative imaging, economics questionnaire
Intervention	Operation notes and photographs; or PHT log. Complications records 6 weeks post start of intervention. Postoperative MRI (surgery intervention only)
6 months	iHOT-33, SF-12, EQ-5D, resource usage, adverse events
12 months (primary outcome)	iHOT-33, SF-12, EQ-5D, patient satisfaction, resource usage, adverse events
2 years	Further procedures questionnaire
3 years	Further procedures questionnaire
5 and 10 years	Linkage to National Joint Registry and HES to identify need for hip replacement

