### Primary outcome

The primary outcome measure is hip pain, function and hip-related quality of life using the **International Hip Outcome Tool-33** (iHOT-33) at 12 months following randomisation. iHOT-33 is a validated hip-specific patient-reported outcome tool which measures health-related quality of life in young, active patients with hip disorders.^21^ It consists of the following domains: symptoms and functional limitations, sports and recreational activities, job-related concerns and social, emotional and lifestyle concerns.

We chose it following our feasibility and pilot study as:
It is more sensitive to change than other hip outcome tools,^21^It does not show evidence of floor or ceiling effects in patients undergoing hip arthroscopy,^21^Patients were involved extensively in item generation; so we can be confident that it measures what is most important to patients,^21^There is an independently determined minimally clinically important difference (MCID),^21^It is used as the principal outcome measure for the UK Non-Arthritic Hip Registry; mandated for arthroscopic FAI surgery by the National Institute of Health and Care Excellence (NICE).^10^

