### Sample size calculation

The development work for iHOT-33 reported a mean iHOT-33 score of 66 and an SD of 19.3 in a heterogeneous population with a variety of hip pathologies. The baseline iHOT-33 data from our pilot trial (HTA grant 10/41/02) suggests the target population of patients being considered for hip arthroscopy for FAI have lower scores with less variability, with a mean of 33 and SD of 16. The MCID for iHOT-33 in this population is 6.1 points.^21^

Our sample size calculation is therefore based on an SD of 16 and a between-group MCID of 6.1: a standardised effect difference between groups at 12 months of 0.38. The expected sample size for 90% power to detect an effect size of 0.38 at 12 months, at a 5% significance level, assuming an approximately normal distribution of the iHOT-33 score is 292. Allowing for 15% loss to follow-up at 12 months, we will recruit a sample of 344 participants over 26months in the UK (172 in each group).

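### The abstract makes the primary analysis a change in iHOT-33, the body makes it the 12-month score, and the primary model does not name baseline iHOT-33, which would settle the difference

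*Protocol article*

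**What the plan says.** Two descriptions of the primary analysis stand in the protocol article.

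- Abstract, Methods: "The primary analysis will compare change in pain and function (iHOT-33) at 12 months between the treatment groups".
- Statistical analysis: "The primary analysis will be of differences in hip-related quality of life (iHOT-33) at 12 months between the two treatment groups".

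The other sections side with the second. The Primary outcome section defines the outcome as iHOT-33 twelve months after randomisation and does not mention change. The Sample size calculation is "based on an SD of 16 and a between-group MCID of 6.1". That SD comes from pilot baseline scores, "with a mean of 33 and SD of 16", so it is the SD of a score and not of a change.

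The Statistical analysis section describes a mixed model with recruiting site as a random effect, treatment as a fixed effect, and "patient characteristics that may prove to be important moderators of treatment effect such as age, gender and FAI type". Baseline iHOT-33 is not named there. It will be available: the recruitment section says that "prior to treatment allocation, baseline patient reported outcomes will be collected", and the baseline row of Table 1 includes "iHOT-33, SF-12,EQ-5D Preoperative imaging, economics questionnaire". The Randomisation section minimises on site and impingement type only, so the design does not balance baseline iHOT-33.

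**The concern.** A change analysis and a score analysis of the same data generally give different estimates and different standard errors unless baseline is in the model. A reader of the abstract and a reader of the body could each hold the trial to a different primary result. If the correlation between baseline and 12-month score is below 0.5, the change analysis is less precise than the sample size assumes. If it is above 0.5, the score analysis forgoes precision that a change analysis would have had. Either way, a chance difference between the arms at baseline feeds into the unadjusted estimate.

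The covariate wording does not close the gap. It brings characteristics in because they might moderate the treatment effect. The usual reason for adjusting a primary model is that a variable predicts the outcome, and baseline score is the natural candidate on that ground.

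**Working it through.** **Inputs.** From the Sample size calculation: difference 6.1, SD 16, effect size 0.38, power 90%, 5% significance, 15% loss, 292 analysable, 344 recruited. From the Statistical analysis section: two-sided tests. From the Randomisation section: 1:1 allocation. Assumptions, not in the document: a correlation rho between baseline and 12-month iHOT-33, shown as a range, and the same SD of 16 at both times. Site effects and the other covariates are left out.

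**The plan's own figure.** n per arm = 2 × (1.960 + 1.282)² / 0.38² = 145.5, rounded up to 146, so 292 in total. Then 292 / 0.85 = 343.5, rounded up to 344. Both figures reproduce, and they correspond to a comparison of 12-month scores without baseline adjustment.

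**Three analyses at 146 per arm** (two-sample t-test, difference 6.1):

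- 12-month score: SD = 16, power 90.1% at any rho.
- Change: SD = 16 × √(2(1 − rho)).
- 12-month score adjusted for baseline (ANCOVA): residual SD = 16 × √(1 − rho²).

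| rho | SD of change | Power, change | Residual SD, ANCOVA | Power, ANCOVA |
|---|---|---|---|---|
| 0.2 | 20.24 | 72.8% | 15.68 | 91.2% |
| 0.3 | 18.93 | 78.3% | 15.26 | 92.6% |
| 0.4 | 17.53 | 84.2% | 14.66 | 94.3% |
| 0.5 | 16.00 | 90.1% | 13.86 | 96.3% |
| 0.6 | 14.31 | 95.3% | 12.80 | 98.2% |
| 0.7 | 12.39 | 98.7% | 11.43 | 99.5% |

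The change analysis matches the planned power at rho = 0.5, falls short below it and gains above it. The adjusted analysis is at or above the planned power throughout.

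**Chance imbalance.** The standard error of the baseline difference between arms is 16 × √(2/146) = 1.87 points. Take an imbalance of 1.96 standard errors, 3.67 points, and rho = 0.5. The score estimate is expected to move by rho × 3.67 = +1.8 points, and the change estimate by (rho − 1) × 3.67 = −1.8 points. In that trial the two estimates would lie about 3.7 points apart, against a target difference of 6.1. Over repeated randomisations both shifts average to zero.

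**Why baseline adjustment settles it.** Write Y for the 12-month score, B for baseline and T for treatment. The model Y − B = a + τT + bB is the same as Y = a + τT + (b + 1)B. The treatment coefficient τ is identical, so with baseline as a covariate it no longer matters whether the outcome is called a score or a change.

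**The case against.** The strongest reply is that the conflict amounts to one word in an abstract. The three operative sections agree on the 12-month score, and the sample size fits that analysis. The covariate list is introduced by *such as*, so it is open and excludes nothing. The article refers to a statistical analysis plan, which is not shown, and a final covariate list is commonly left to it. All of this stands. It limits the point to a reconciliation and a recommended improvement.

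Four stronger readings are tempting, and the documents do not support them.

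- *The plan leaves baseline out.* It does not name baseline iHOT-33 in the model. An open list and an unseen analysis plan do not show that it is excluded.
- *The estimate would be biased.* Under randomisation with complete data, the score and change analyses both estimate the same mean difference without bias. Chance imbalance is already reflected in the standard error.
- *The trial is too small.* The 292 and 344 are correct for the score analysis. Nothing in the document places rho below 0.5, so a shortfall under a change analysis is possible but not shown. The section also reports an SD of 19.3 from a heterogeneous hip population and sets it aside; whether 16 is the right SD is a separate question.
- *The model will contain treatment interactions, or covariates chosen from outcome data.* The moderator wording permits either reading, but no interaction term and no selection procedure is described. Age, gender and FAI type are named in advance, and moderation by FAI type is planned separately as a subgroup analysis.

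What survives is that the printed texts differ, and that the stated ground for entering covariates is possible moderation, which does not itself bring baseline score in.

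**Conclusion.** The point holds as a matter of precision and clarity. The abstract and the body describe different primary analyses, and the primary model as printed does not name the one covariate that would make them equivalent. At the plan's own difference, SD and analysable number, power is 90% for the score and about 73% to 99% for the change as rho runs from 0.2 to 0.7. For the baseline-adjusted analysis it is 91% to 99.5%. These figures rest on an assumed correlation and on equal SDs at the two times, so no single loss or gain can be claimed. The planned sample size is not called into question, and the validity of the randomised comparison is not at risk. This is an improvement worth making, not a defect that undermines the trial.

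**What to change.** Use one definition in the abstract and the Statistical analysis section: the between-group difference in 12-month iHOT-33, estimated from the mixed model with fixed main effects of treatment, baseline iHOT-33, FAI type, age and gender, and a random effect of site. Replace the moderator wording with a statement that these are pre-specified prognostic covariates. Leave moderation by FAI type to the subgroup analysis that the section already plans.

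The cost is wording in the protocol and the statistical analysis plan. Baseline iHOT-33 is already collected, so no new data and no change to the sample size are needed. The Data management section says that outcomes are not analysed until all primary outcome data are in, so the change can be recorded before any outcome result is seen.

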### Randomisation

Participants will be randomised, in a 1:1 ratio, to arthroscopic surgery or PHT using a computer-generated sequence. Allocation will be made by the research nurse/associate via a centralised telephone randomisation service provided remotely by WCTU. Allocation concealment will be ensured, as the randomisation programme will not release the randomisation code until the patient has been recruited into the trial. In order to improve baseline balance between intervention group samples, a minimisation (adaptive stratified sampling) algorithm will be implemented using study site and impingement type (cam, pincer or mixed) factors. Research nurses/associates who recruit participants will ensure they are referred for the allocated intervention. Patients and clinicians cannot be blind to treatment allocation. However, outcome assessors will be blind to the treatment delivered.

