### Risks and benefits

Both interventions are thought to provide benefit in patients with FAI. The short-term risks of this study relate to the two interventions. These risks are described below and inform the expected serious adverse events (SAEs).

Hip arthroscopy requires a general anaesthetic. The risk of complications from hip arthroscopy is about 1–2%. These include:
Infection—thought to be <1 in 1000.Bleeding—possibly causing bruising or a local haematoma.Traction-related—in order to perform hip arthroscopy, traction is required to separate the hip joint surfaces. Sometimes after the procedure, the pressure from the traction can cause some numbness in the leg. The numbness usually resolves within a few hours or days.Osteonecrosis—during surgery, the blood supply to the hip joint could be damaged. However, there are no reported cases of osteonecrosis following arthroscopic FAI surgery.Femoral neck fractures—this is also a very rare complication. This complication would require a further procedure to fix the fracture.

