#### Personalised hip therapy

There are some small risks with pain medications and joint injection. However, the main risk is muscle soreness and transient increases in pain from the exercises that will be undertaken.

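### For intervention complications the only stated effect measure is an adjusted odds ratio, which is likely to be very imprecise, and has no finite positive value if either arm has no events, at the protocol's own 1–2% surgical risk

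*Protocol article*

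**What the plan says.** The Statistical analysis section of the protocol article treats adverse events, complications related to the trial interventions and the need for further procedures as one family of dichotomous outcomes. It plans χ² or Fisher's exact tests, and adds that "mixed-effects logistic regression analysis will be undertaken, adjusting for the stratifying variables, with differences between trial intervention groups quantified as ORs", with 95% CIs. The stratifying variables come from the Randomisation section, where minimisation "will be implemented using study site and impingement type (cam, pincer or mixed) factors". The abstract gives 24 hospitals.

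Under Risks and benefits the protocol says of surgery: "The risk of complications from hip arthroscopy is about 1–2" per cent. For PHT it gives no rate, only a description: "There are some small risks with pain medications and joint injection", and "the main risk is muscle soreness and transient increases in pain from the exercises that will be undertaken". On numbers, the Sample size calculation section says "we will recruit a sample of 344 participants over 26months in the UK (172 in each group".

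**The concern.** The method is suited to outcomes with a fair number of events in both arms. Intervention complications may not be such an outcome. With a handful of events over 24 sites and three impingement types, the adjustment terms have little to rest on. If one arm has no events, the odds ratio has no finite positive value at all.

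The model sentence carries no condition on event numbers. Elsewhere the same section does qualify its methods: the time-to-event analysis of adverse events, and the grouping by physiotherapist and surgeon, are each planned only if the data suit them.

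At stake is how the harms of surgery are set against those of physiotherapy. The reader of the results may be left with a p value and either no effect estimate or one with an interval too wide to use.

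**Working it through.** **Inputs from the protocol.** Arthroscopy complication risk 1–2% (Risks and benefits); 344 randomised, 172 per arm, 15% loss (Sample size calculation); 24 sites (abstract); three impingement types (Randomisation). **Assumed:** the PHT complication rate, taken over a range from 0.1% to 5%.

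**The plan's own sample size.** 6.1/16 = 0.38. The normal-approximation formula with d = 0.38, 90% power and two-sided 5% gives 292, and 292/0.85 = 343.5, so 344. Both stated figures are reproduced. The sample size is set for iHOT-33; the article states no expected number of complications.

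**Expected surgical complications.** n × risk:
- 172 × 0.01 = 1.7; 172 × 0.02 = 3.4.
- 95% binomial range: 0 to 5 at 1%; 0 to 7 at 2%.
- Chance of none, (1 − p)^172: 0.99^172 = 18%; 0.98^172 = 3%.

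**Chance that at least one arm has no events.** 1 − (1 − a)(1 − b), where a = (1 − p_surgery)^172 and b = (1 − p_PHT)^172. For example, with 2% and 0.5%: a = 0.031, b = 0.422, and 1 − 0.969 × 0.578 = 0.44.

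| Assumed PHT rate | Surgery 1% | Surgery 2% |
|---|---|---|
| 0.1% | 87% | 85% |
| 0.5% | 52% | 44% |
| 1% | 32% | 20% |
| 2% | 20% | 6% |
| 5% | 18% | 3% |

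If PHT has no events and surgery has some, the odds ratio is infinite. In the reverse case it is zero. If neither arm has any, it is undefined.

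**Precision when both arms have events.** For 3/172 against 1/172 the unadjusted odds ratio is (3/169)/(1/171) = 3.04. The standard error of its log is √(1/3 + 1/169 + 1/1 + 1/171) = 1.16, so the Wald 95% CI is about 0.3 to 29.

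**The model itself.** A random-intercept logistic model (24 sites, arm, three impingement types) was fitted to 150 simulated trials per scenario, with an assumed type mix of 75/8/17%. The treatment log-odds diverged in 99–100% of runs with no PHT events, and in 55%, 14% and 6% of runs at 2% against 0.5%, 1% and 2%. In those last three scenarios the share of diverging runs equals the share with an empty arm. With 150 runs these shares are noisy, and the exact table above is the better guide. At 2% against 0–2%, at least one impingement type had no events in 72–93% of runs. At an illustrative 10% against 5% (about 26 events) the odds ratio was finite in every run. The simulated data had no true site variation, so they say nothing about how well the site variance would be estimated.

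**What Fisher's test supplies.** Against 0/172, the p value is 0.50 for 2 events, 0.25 for 3, 0.061 for 5 and 0.030 for 6. It can always be computed, but it gives no effect size. The chance of five or fewer surgical events is 99% at 1% and 87% at 2%.

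**What a risk difference supplies.** For 3/172 against 0/172 the difference is 1.7%. The Wilson limits are 0.6% and 5.0% for surgery, and 0 and 2.2% for PHT. Newcombe's interval is then 1.74 − √(1.15² + 2.18²) to 1.74 + √(3.26² + 0²), that is −0.7% to 5.0%. It is finite and readable although one arm has no events.

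**The case against.** A reader might infer that the complications model cannot be estimated at all, because only two or three events will occur. The protocol does not support that. The 1–2% is for arthroscopy alone, whereas the outcome covers complications of both interventions, and Table 1 places the six-week complications record in the intervention row that serves both arms. Two or three is the surgery-arm expectation; it is the trial total only if PHT has no events, which the protocol does not say. Patients who cross over to surgery, and the pooled pilot patients (number not given), could add events too. Failure is certain only when an arm is empty. Site enters the section's mixed-model strategy as a random effect, so 24 hospitals cost one variance term, and a variance estimated as zero leaves an ordinary logistic regression rather than no fit.

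Nor does the point reach the whole safety comparison. The same sentence covers all adverse events and further procedures, for which no rate is given. The section also provides Fisher's test for sparse tables and, for adverse events, graphs and a possible Kaplan–Meier analysis of overall and class-specific risk.

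Finally, a rule for sparse events may sit in the statistical analysis plan, which is not shown, and its absence from a journal article is no fault. That stands: a penalised-likelihood fallback or a numerical event threshold belongs in that plan. What remains is narrower. The article does name an effect measure for complications, without qualification, and that measure fits poorly with the risk the article itself quotes. Fisher's test does not fill the gap, since it returns only a p value, and the Kaplan–Meier analysis is conditional and is not stated as an effect measure for complications.

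**Conclusion.** The point holds in a limited form, as a cheap improvement to a secondary analysis. At 1–2% the surgery arm expects about two to three complications in 172, plausibly 0 to 7. The adjusted odds ratio for intervention complications is therefore likely to be very imprecise. With surgery at 2%, the chance that it has no finite positive value runs from 85% to 3% as the assumed PHT rate runs from 0.1% to 5%.

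This rests on the protocol's surgical risk applying to this trial, on 172 analysed per arm, and on a PHT rate that the protocol does not give. If PHT complications are as common as 5%, an empty arm is unlikely and the remaining problem is mainly imprecision. The primary analysis is untouched.

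**What to change.** For intervention complications and other rare events, state the proportion in each arm and the risk difference with a Newcombe or exact 95% CI as the effect measure, beside Fisher's exact test. List surgical and PHT-specific events separately, since they differ in kind. Keep the adjusted mixed-effects odds ratio for dichotomous outcomes with enough events in both arms, and leave the definition of enough, and any fallback estimator, to the statistical analysis plan.

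The cost is a change of wording, with no new data and no change in sample size. The downside is that the rare-event estimate is not adjusted for site and impingement type. With so few events, little useful adjustment is lost.
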